#### Criteria for discontinuing or modifying allocated interventions {11b}

A study participant will be discontinued from participation in the study if:Withdrawal of consent by subject or parent of cohort subject.Cohort subject is non-resident for a significant portion of the malaria transmission season.Cohort subject is not available for follow-up visits (i.e., lost to follow-up).Subject experiences any clinically significant adverse events (AEs), laboratory abnormalities, or other medical conditions or situations such that continued participation in the study would not be in the best interest of the subject. This includes events that are not related to malaria or the ET intervention.Development of any exclusion criteria.

The reason for participant’s premature termination will be documented on the appropriate page of the data collection forms and specified which of the following possible reasons were responsible for the study’s premature termination:Serious adverse event (SAE); any events that are life-threatening or result in death, events that result in hospitalization or prolongation of existing hospitalization, events that result in persistent or significant debilitation or incapacity.Participant’s consent withdrawal.Lost to follow-up: A “lost to follow-up” is any participant who completed all protocol-specific procedures up to the administration of the investigational product or intervention, but was then lost during the study period to any further follow-up, with no safety information and no endpoint data.Any other reason requiring a premature termination of the participant.

All study participants are free to withdraw from the study at any time without giving a reason. If a subject voluntarily withdraws or is withdrawn by the Principal Investigator (PI) during the study, data from their follow-up until that date will be used towards incidence analyses. A 20% LTFU was included in the sample size calculations, so there will be no new children recruited as replacement for follow-up during the study.

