### Outcomes {12}

The primary outcome measure is the incidence rate of malaria infection as measured by active infection and clinical malaria case detection in cohorts of 55 children (between 6 months and 10 years old) per cluster, 17 clusters per arm on a biweekly basis in peak transmission season and monthly basis in low transmission season. [Time Frame: 24 months].

Secondary outcome measures include:Clinical malaria incidence measured in children between 6 months and 10 years old living in the study cohorts using passive case detection via the existing community health workers and health centers. [Time Frame: 24 months]Malaria parasitemia measured in children between 6 months and 10 years old in the cohorts of 55 children. [Time Frame: 24 months]Prevalence of moderate (defined as 7–9.9 g/dL hemoglobin) to severe anemia (< 7 g/dL hemoglobin) measured in children under 5 years of age in the cohorts of 55 children four times: at the start and end of the rainy season (April and November respectively) of Year 1 and Year 2. [Time Frame: 24 months]Mean numbers of female malaria mosquitoes (*An. gambiae s.l., Anopheles funestus s.l.*) captured in study houses measured by CDC light traps in 20 clusters, 10 houses per cluster on a monthly basis. [Time Frame: 24 months]Malaria parasite sporozoite rate assessed in 10% of all anophelines captured by CDC light trap. [Time Frame: 24 months]Entomological inoculation rates measured in each study arm as the product of the anopheline vector density and sporozoite rate. [Time Frame: 24 months]

Other pre-specified outcome measures include:7.Cost modeling will assess the cost-effectiveness of EaveTubes compared to the previously applied Screening + EaveTubes intervention, and compared to other vector control interventions such as long-lasting insecticide nets and indoor residual spray. [Time Frame: 24 months]8.Assessments of willingness to participate and adoption of EaveTubes at the end of the study period through questionnaires and willing-to-pay surveys. [Time Frame: 24 months]

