##### Primary

Protective efficacy (PE) against clinical malaria infection will be determined by comparing hazard rates of malaria clinical cases between the two treatment arms based on an intention to treat (ITT) analysis. The primary hypothesis on PE against overall malaria case incidence will be tested by comparing the hazard rates of the overall malaria case incidence between the control and ET in the ITT population using a proportional hazards model. The model will include relevant individual-level, household-level, and cluster-level baseline covariates, treatment assignment, and follow-up visits and random effects to account for correlations among the subjects within the same cluster and among multiple infections within the same individual. The hazard ratio $$\beta$$ between ET and control will be estimated, along with a 95% confidence interval. The null hypothesis of PE = 0% is equivalent to $$\beta =0$$, which will be tested by the Wald’s test $$z=\widehat{\beta }/s$$, where $$s$$ is the estimated standard error of $$\widehat{\beta }$$. There will be one formal interim analysis to test the primary hypothesis. The decision boundaries are calculated for either stopping for futility or stop for efficacy using the O’Brien-Fleming error spending function [8–10], with a 2-sided Type I error rate of 0.05, Type-II error rate of 0.2; baseline incidence rate of 1.5 per person-year, and between-cluster CV of 40%. The interim analysis will occur when 658 events (50% information) are collected. Assuming a baseline incidence rate of 1.5 per person-year, the interim analysis is estimated to occur around the end of Year 1 of the intervention follow-up. Due to the formal interim look at the data which costs a certain amount of type-I error rate and type-II error rates, the final critical value is different from what would be for a study without the interim look.

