#### Methods in analysis to handle protocol non-adherence and any statistical methods to handle missing data {20c}

Significant effort will be made to avoid having missing values on outcome (malaria infection status and visit dates, and entomological endpoints). When missing values occur for an outcome for reasons not related to the outcome, reasons for missingness and the missing fraction by treatment arm and cluster will be reported. Per protocol, the subjects are screened actively on the malaria status (the outcome) every 4 weeks.

If a subject misses one or more scheduled visits due to reasons not related to the ETs product or the outcome, the subject will have missing values on the outcome that can be regarded as ignorable missingness (MAR or MCAR [11]).

If a subject drops out study due to reasons unrelated to the ETs product and/or malaria infection, then the missing observations from the subject can be regarded as ignorable missingness (MAR or MCAR [11]).

In both cases, all the available data from the subject will be included in the primary and secondary analysis, without employing any specific missing data analysis techniques, due to the ignorability of the missing mechanisms [11].

Missing baseline covariates (individual-level, household-level, and cluster-level) that are a part of the regression models for the outcome of interest will be imputed using simple hot-deck imputation methods if the missing fraction for the covariate is < 5%. If the missing fraction for a covariable is ≥ 5%, appropriate multiple imputation approaches will be applied. If ≥ 50% of the subjects have missing values on a covariate (due to missing at random or missing completely at random), that covariate will be excluded in the model.

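### Section 11b ends a child's participation in the study, not just the intervention, for illness-related reasons; the resulting outcome-related censoring is avoidable, although its bias on the primary hazard ratio is probably small and toward no effect

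*Protocol article*

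**What the plan says.** The section is headed as discontinuing or modifying the allocated intervention, but its list opens with "A study participant will be discontinued from participation in the study if". Two of the listed triggers concern health:

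- "Subject experiences any clinically significant adverse events (AEs), laboratory abnormalities, or other medical conditions or situations", with the condition "such that continued participation in the study would not be in the best interest of the subject". The text adds that events unrelated to malaria or the ETs are included.
- "Development of any exclusion criteria", with no such condition. The individual-level exclusions in Eligibility criteria {10} include a baseline haemoglobin of 7 or below, known chronic disease and signs of clinical decompensation.

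For a child who withdraws or is withdrawn by the principal investigator, "data from their follow-up until that date will be used towards incidence analyses", and no replacement is recruited.

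The primary comparison of hazard rates is "based on an intention to treat (ITT) analysis". The missing-data section {20c} regards dropout as ignorable in this case: "If a subject drops out study due to reasons unrelated to the ETs product and/or malaria infection". It describes no handling for dropout that is related to either. Outcomes {12} lists moderate to severe anaemia as a secondary outcome, "measured in children under 5 years of age in the cohorts of 55 children four times".

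**The concern.** ETs are cemented into the house wall, and nothing in the protocol says they are taken out when a child is discontinued. Removal therefore changes neither the exposure of an ET child nor the non-exposure of a control child. It only ends observation.

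The reasons for removal can be consequences of malaria or anaemia, which are the outcomes under test. If ETs work, more high-risk children would be removed in the control arm than in the ET arm. The control arm then looks healthier than it is, and the hazard ratio moves toward 1. In the anaemia surveys, the children lost could be those most likely to be anaemic again. The 20% allowance for loss to follow-up protects the number of events, not the validity of the comparison when loss depends on the outcome.

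**Working it through.** **1. The plan's own figure.** Inputs from Sample size {14}: control hazard 1.5 per person-year, PE 35% (hazard ratio, HR, 0.65), 2 years, 20% loss, 17 × 55 = 935 children per arm, coefficient of variation 0.40.

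- First events with exponential times: 0.8 × 935 × [(1 − e^−3) + (1 − e^−1.95)] = 748 × (0.9502 + 0.8577) = 1352. With cluster frailty at 0.40 the count is 1294 (gamma) or 1300 (lognormal). The plan states 1315, so all three are within 3%.
- Clusters by the Hayes–Bennett formula, with 55 × 0.8 × 2 = 88 person-years per cluster: 1 + 7.849 × [(1.5 + 0.975)/88 + 0.16 × (1.5² + 0.975²)]/0.525² = 16.4. Seventeen per arm gives 81.5% power, or 81.1% with the final critical value 1.9744.

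The sample size is not at issue.

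**2. Hand calculation of the bias.** The documents give no rate of health-related discontinuation, so these inputs are assumptions: 2% or 5% of control children removed at mid-follow-up, 65% as many in the ET arm, and removed children at three times the average rate. If a fraction f of person-time is lost, the observed rate relative to the true rate is (1 − 3f)/(1 − f).

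- 2% removed: control f = 0.02 × 0.5 = 0.010 gives 0.9798; ET f = 0.0065 gives 0.9869. HR = 0.65 × 0.9869/0.9798 = 0.655, PE 34.5%.
- 5% removed: control f = 0.025 gives 0.9487; ET f = 0.01625 gives 0.9670. HR = 0.65 × 0.9670/0.9487 = 0.6625, PE about 33.7%.

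**3. Simulation of recurrent episodes.** Also on assumed inputs: 400,000 children per arm, rate 1.5 × HR × child frailty (gamma, mean 1, variance 0.5 or 1), and each episode leading to discontinuation with probability q, either constant or proportional to the child's frailty. The estimate is the crude rate ratio; the true value is 0.65.

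| q per episode | Estimated ratio | Control children removed | ET children removed |
|---|---|---|---|
| 0 | 0.647–0.653 (simulation noise) | 0 | 0 |
| 0.5% | 0.651–0.655 | 1.5–2.8% | 1.0–1.8% |
| 1% | 0.650–0.661 | 2.9–5.1% | 1.9–3.5% |
| 2% | 0.652–0.669 | 5.7–9.1% | 3.7–6.5% |
| 5% | 0.658–0.682 | 13.1–17.7% | 8.9–13.3% |
| 10% | 0.666–0.695 | 23.0–27.4% | 16.3–21.0% |

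Removal is differential and the shift is toward no effect. It stays at or below about 0.02 on the ratio scale up to q = 2%.

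**4. Anaemia.** This applies only if a later low haemoglobin leads to removal, which the text leaves unclear. Assume a baseline logit of −1.5, a within-child odds ratio of 0.65, one in ten anaemic children severe and removed, four surveys, and a between-child standard deviation of 1 or 2. At the fourth survey, control prevalence falls from 22.1% to 21.4% (SD 1) or from 28.5% to 26.3% (SD 2). The population odds ratio barely moves: 0.687 to 0.692, and 0.757 to 0.759. Under this model the loss distorts the prevalence more than the comparison.

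**5. The haemoglobin wording.** Eligibility criteria {10} ties the exclusion to baseline and prints the unit as mg/dL. Section 11b speaks of developing a criterion, which can only happen later. Outcomes {12} counts severe anaemia below 7 g/dL as an outcome at repeated surveys. Read together, they do not settle whether a low value at a later survey ends participation.

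**The case against.** A reader might infer several stronger things from section 11b. The text does not support them.

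- *That any significant adverse event or abnormal laboratory value removes the child.* The clause is conditional on the child's best interest. Only the exclusion-criterion clause is unqualified.
- *That a child found severely anaemic at a survey is removed.* The haemoglobin exclusion is a baseline one, and the anaemia analysis provides random effects for repeated episodes in one child, which points the other way.
- *That hospitalisation for severe malaria is itself a trigger.* The SAE entry belongs to a list for recording why a termination happened. The follow-up section refers severely ill children to a clinic and treats a treated child as not at risk for two weeks; it does not mention removal.
- *That safety follow-up stops.* Adverse event reporting {22} has SAEs recorded for the whole trial and managed with follow-up, and the data cut-off in section 11b concerns the incidence analyses. What remains is that section {22} does not say whether discontinued children are covered.
- *That the primary analysis is no longer intention-to-treat.* Analysing children as randomised, with time censored at withdrawal, is still ITT. Informative censoring is a separate question.

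It can also be said that the bias is small, that the within-child random effect absorbs part of it when withdrawal depends only on observed past episodes, and that the unseen analysis plan may deal with outcome-related dropout. All of this stands and limits the size of the point. It does not answer it: the rule that stops observation is written in the protocol, and no analysis recovers data that were never collected.

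**Conclusion.** The point holds in a limited form. Section 11b makes illness, or the development of a health-related exclusion criterion, a reason to stop observing a child whose exposure does not change, and the stated ignorability assumption does not reach such children when the reason is related to malaria or the ETs. This is outcome-related censoring that the design could avoid.

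The effect on the primary result is probably small and conservative: PE of about 34% instead of 35%. It reaches roughly 30.5–33.4% only if one episode in ten leads to discontinuation. These figures rest on assumed removal rates and frailty, since the documents give none. The stronger reason to act is the possible loss of severe-anaemia and SAE information from the children who carry most of it. How far that loss goes depends on two points the protocol leaves unclear: the later haemoglobin value, and SAE recording after discontinuation. The change is worth making, but the trial's conclusion does not hang on it.

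**What to change.** Amend section 11b to separate two decisions. Keep the best-interest provision for study procedures. State that children discontinued for health reasons, or for a health-related exclusion criterion, remain under active and passive malaria detection, haemoglobin surveys and SAE follow-up where consent allows. Let this observation end only on withdrawal of consent, death, permanent move or loss. Analyse these children as randomised, and report health-related discontinuations by arm and cluster. A sensitivity analysis for informative censoring would cover those who are still lost.

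Reconcile Eligibility criteria {10}, section 11b and Outcomes {12} on whether a post-baseline haemoglobin of 7 or below counts as developing an exclusion criterion, and on its unit. State in section {22} whether SAE recording covers discontinued children.

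Deleting the best-interest clause or every exclusion-criterion trigger would go too far; joining another drug or vaccine trial, for example, is also an exclusion criterion. Decisions on clinical care stay with the investigators. The cost is a short amendment and a few more visits to enrolled children in villages that are visited anyway.

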#### Strategies to improve adherence to interventions {11c}

The status of the intervention (damage to ETs) and general condition of all houses will be monitored by quarterly village walk-throughs by project staff in both study arms. In addition, a designated member of the study team will be available for householders to report ET-related construction problems and get them fixed during the trial.

The persistence of the chemical insecticide used on the inserts will be monitored bimonthly by taking a sample of inserts from the treated villages to the lab (these will be replaced with fresh inserts) and exposing mosquitoes to them in a controlled bioassay. We will use F1 adult female anopheline mosquitoes reared from field-collected eggs in WHO cone tests with a 3-min exposure and mortality monitored 1 day post-exposure. Mortality will be compared against equivalent mosquitoes (wild-type resistant) exposed to untreated “control” inserts. Inserts will be replaced once the mortality post-exposure falls below 70% (from previous results, we expect this to be every 10–12 months).

During ET insert retreatment rounds, the number and quality of the retrieved inserts will be monitored as an indicator of product quality and intervention adherence.

#### Relevant concomitant care permitted or prohibited during the trial {11d}

While the standard-of-care for clinical management of malaria and vector control interventions (e.g., LLINs, IRS) will not be withheld in either the study arm, these interventions will be monitored and recorded throughout the trial. At baseline, children enrolled into the cohorts will be provided a 3-day course of standard, first-line antimalarials (Coartem® or ASAQ Winthrop®, both Artemisinin combination therapies (ACTs) recommended by the NMCP in Côte d’Ivoire) to clear any malaria parasite infections as well as a new LLIN. In addition, subjects will be provided treatment for malaria infection throughout the follow-up period. Lastly, participants will be encouraged to continue LLIN use and not instructed to avoid alternative vector control tools (e.g., coils, topicals, aerosol sprays, repellents) which will allow for an estimation of the ET effect assuming all other measures are still occurring for malaria prevention, essentially providing insight on an additive benefit above that provided by currently recommended WHO malaria preventive measures.

#### Provisions for post-trial care {30}

Not applicable—the study will not provide post-trial care.

### Outcomes {12}

The primary outcome measure is the incidence rate of malaria infection as measured by active infection and clinical malaria case detection in cohorts of 55 children (between 6 months and 10 years old) per cluster, 17 clusters per arm on a biweekly basis in peak transmission season and monthly basis in low transmission season. [Time Frame: 24 months].

Secondary outcome measures include:Clinical malaria incidence measured in children between 6 months and 10 years old living in the study cohorts using passive case detection via the existing community health workers and health centers. [Time Frame: 24 months]Malaria parasitemia measured in children between 6 months and 10 years old in the cohorts of 55 children. [Time Frame: 24 months]Prevalence of moderate (defined as 7–9.9 g/dL hemoglobin) to severe anemia (< 7 g/dL hemoglobin) measured in children under 5 years of age in the cohorts of 55 children four times: at the start and end of the rainy season (April and November respectively) of Year 1 and Year 2. [Time Frame: 24 months]Mean numbers of female malaria mosquitoes (*An. gambiae s.l., Anopheles funestus s.l.*) captured in study houses measured by CDC light traps in 20 clusters, 10 houses per cluster on a monthly basis. [Time Frame: 24 months]Malaria parasite sporozoite rate assessed in 10% of all anophelines captured by CDC light trap. [Time Frame: 24 months]Entomological inoculation rates measured in each study arm as the product of the anopheline vector density and sporozoite rate. [Time Frame: 24 months]

Other pre-specified outcome measures include:7.Cost modeling will assess the cost-effectiveness of EaveTubes compared to the previously applied Screening + EaveTubes intervention, and compared to other vector control interventions such as long-lasting insecticide nets and indoor residual spray. [Time Frame: 24 months]8.Assessments of willingness to participate and adoption of EaveTubes at the end of the study period through questionnaires and willing-to-pay surveys. [Time Frame: 24 months]

### Participant timeline {13}

The duration of the current study is 2 years and 9 months. The first 6 months are for set up and baseline. The cRCT proper runs for 2 years with an additional 3 months for primary data analysis.

The epidemiological monitoring will require 1 to 2 visits per month, depending on the time of year (1 visit per month from November until April, and 2 visits during the peak season from May until October). The epidemiological monitoring visits are expected to last approximately 30 min, with an additional 30 min twice a year for anemia and respiratory testing.

The entomological monitoring will require 3 nights (6 pm–8 am) per house each month. ET installations will require approximately 3 months for an estimated 3000 households in 17 village clusters. Retreatment of netting inserts takes approx. 10 min per house and is done from the outside of the house.

**Table Tabb:** 

Study period				
	**Pre-trial**	**Baseline**	**Follow up**	**End of trial**
**Timepoint**	T_(Jan 2023–Feb 2023)_	T_(Mar 2023–Jun 2023)_	T_(Jul 2023–Jun 2025)_	T_(Jul 2025–Sept 2025)_
**Ramp-up**				
Village selection	X			
Community engagement	X			
Census	X			
Village randomization and allocation	X			
**Enrollment**				
Informed Consent		X		
Screening		X		
ET installation		X		
Distribution of LLINs		X		
Baseline prevalence study		X		
Parasite clearance		X		
**Intervention**				
Epidemiological monitoring (active case detection)			X	
Entomological monitoring			X	
Intervention monitoring and replacements			X	
**Assessments**				
Baseline Analysis		X		
Final Analysis				X

### Sample size {14}

The number of villages for the cRCT is estimated at 17 per treatment arm based on the power analysis which is detailed in the Statistical Analysis Plan.

The sample size determination on the required number of households per cluster for testing the primary hypothesis on PE is based on the hazard rate comparison in the proportional hazards regression model. With the following specifications: power = 80%, 2-sided type-I error rate = 5%.True PE/Minimum effect size = 35%Baseline first-time malaria infection hazard rate = 1.5 cases of falciparum malaria per person-year (conservative estimate based on control arm data from first SET cRCT)Coefficient of variation (k) = 40% (based on first SET cRCT)Loss to follow-up (LTFU) rate = 20%Monitoring = 2 years to capture 2 peak transmission seasonsOne interim analysis for efficacy and non-binding futility with the O’Brien-Fleming error spending function when 50% information is collected

With 17 clusters per treatment, 55 children (aged 0.5 to 10 years old) from 55 different households per cluster are expected to yield 1315 independent first-time malaria events with a 24-month follow-up period to yield 80% power in testing the primary hypothesis on PE. Since the sample size already factors in a 20% LTFU rate, there is no need for replacement subjects.

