**Incidence rate**

The malaria incidence rate is defined as the ratio of the number of new malaria cases during the follow-up period vs the sum of the time at risk (in year) across the individuals within the same cluster. The incidence rates per person-year during the whole intervention follow-up will be calculated by cluster in the ET and the control arms respectively. Summary statistics of the cluster-level incidence rate will be provided by treatment arm; the incidence ratio between the two arms will be also calculated.

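### The stated 1315 events and the 658-event interim trigger count first malaria events, but the primary model analyses every episode

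*Protocol article*

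**What the plan says.** Sample size {14} enters the control rate as "Baseline first-time malaria infection hazard rate = 1.5 cases of falciparum malaria per person-year". It concludes that the design is "expected to yield 1315 independent first-time malaria events with a 24-month follow-up period", giving 80% power for the primary hypothesis on protective efficacy (PE). It refers the power analysis for the number of villages to the SAP, which is not shown.

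The Primary subsection of the statistical methods tests that hypothesis on the overall incidence of malaria cases, using a proportional hazards model with "random effects to account for correlations among the subjects within the same cluster and among multiple infections within the same individual". The opening of the same methods section takes a child out of the risk set for two weeks after any malaria treatment, and Epidemiological monitoring repeats the rule. The Incidence rate subsection defines the rate as "the ratio of the number of new malaria cases during the follow-up period vs the sum of the time at risk". Outcomes {12} names an incidence rate without saying whether first or all episodes count.

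The Primary subsection also sets one interim analysis at 658 events, equated with half of the information. It uses the 1.5 per person-year again, this time as a baseline incidence rate and without the first-time label.

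**The concern.** A first-event analysis lets each child contribute at most one event. A random effect for several infections in one child, and a rule that returns the child to risk after two weeks, have a purpose only if later episodes count. The sizing and the test of the same hypothesis therefore use different event sets, and no section reconciles them.

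Two things are at stake. The headline event count may not describe the analysis that will be run. More practically, the interim trigger is half of 1315, and whoever runs the interim cannot tell from the protocol whether to count first events or all episodes. Whether an event is an infection or a clinical case is a separate question and is left aside here.

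**Working it through.** **Inputs (Sample size {14} unless noted).** 17 clusters per arm and 55 children per cluster, so 935 children per arm. Loss to follow-up is 20%, leaving 0.8 × 935 = 748 per arm (44 per cluster). Control rate 1.5 per person-year; PE 35%, so the ET rate is 0.65 × 1.5 = 0.975. Follow-up 2 years; between-cluster k = 0.40. Final critical value 1.9744 and interim at 658 events (Primary subsection).

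**1. Reproducing 1315.** With one event per child:

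748 × [(1 − e^−3.0) + (1 − e^−1.95)] = 711 + 642 = 1352, which is 2.8% above 1315.

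Averaging over between-cluster variation with k = 0.40 gives 1300 (lognormal) or 1294 (gamma). So 1315 is a first-event count.

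**2. All episodes, same inputs**, with 1.5 read as the rate for every episode:

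- No off-risk window: 748 × 2 × (1.5 + 0.975) = 3703.
- With the two-week window (2/52 year per episode): 1496 × [1.5/(1 + 1.5 × 2/52) + 0.975/(1 + 0.975 × 2/52)] = 1496 × (1.418 + 0.940) = about 3527.

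The ratio to first events runs from 3527/1352 = 2.6 to 3703/1315 = 2.8.

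**3. Power at PE 35%.**

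*Cluster rate formula:* power = Φ(√{17 × (1.5 − 0.975)² / [1.5/y0 + 0.975/y1 + k²(1.5² + 0.975²)]} − 1.9744), where y is person-years at risk per cluster.

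- First events: y0 = 44 × 0.950/1.5 = 27.9 and y1 = 44 × 0.858/0.975 = 38.7. The denominator is 0.054 + 0.025 + 0.512 = 0.591, and power is 80.0%.
- All episodes: y0 = y1 = 88. The denominator is 0.028 + 0.512 = 0.540, and power is 83.4%.
- With 16 in place of 17 (the usual small-sample correction): 77.5% and 81.1%.

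*Log hazard ratio form:* SE² = 2k²/17 + 1/d0 + 1/d1, where d is events per arm.

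- First events: 0.01882 + 1/711 + 1/642 = 0.0218, and power is 83%.
- All episodes: 0.01882 + 1/2244 + 1/1459 = 0.0200, and power is 86%.

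In both forms the between-cluster term dominates, so the extra episodes add only about 3 percentage points.

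**4. Interim trigger.**

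- Against first events: 658/1315 = 50%.
- Against all episodes: 658/3703 = 17.8% and 658/3527 = 18.7%.

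The stated timing, about the end of Year 1, does not settle the unit. At constant rates with everyone enrolled, 658 first events arrive at about 5.7 to 6 months and 658 episodes at about 4.3 months. Season or staggered entry could shift both.

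**5. Sensitivity to the meaning of 1.5.** Study setting {9} gives an average of 2 to 3 cases per child per year in the first trial. If that were the control rate for all episodes, the formula with the two-week window gives 1496 × (1.857 + 1.238) = about 4600 to 1496 × (2.690 + 1.814) = about 6700 episodes.

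**The case against.** The strongest reply is that only one analysis is planned. The primary model, the off-risk rule and the incidence definition all point to every episode, and no section describes a first-event analysis. Sizing on independent first events avoids assuming a within-child correlation and gives slightly lower power than the planned test, so 80% can stand as a floor. The SAP may say so. This stands as far as power goes, and it is a legitimate way to size a trial. But the article does not present the sizing as a simplification, and the reply does not rescue the interim trigger, which takes half of the first-event total into a model that counts something else.

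Two stronger readings are tempting. A reader might infer that two different PEs sit under the primary endpoint, with the first-event one resting mainly on Year 1 or pulled towards no effect where children differ in risk. Those would be properties of an analysis the protocol does not plan, and it gives no figure for variation in risk between children. A reader might also infer that Year 2 is a period of waning insecticide. The intervention and adherence sections instead have inserts replaced once bioassay mortality falls below a threshold, with 10 to 12 months as the expected replacement interval.

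It is also fair to object that a replacement count cannot be fixed from the article alone, because the 1.5 is called a first-time hazard in one place and an incidence rate in another.

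**Conclusion.** The inconsistency is real, but its consequence is limited. The 1315 events are first events; the planned test would use about 3500 to 3700 episodes at the plan's own inputs. The 658-event trigger is half of the former and about 18% to 19% of the latter, and its unit is not stated. The trial is not under-powered by this: at the same 35% PE, power is about 83% to 86% for all episodes against 80% to 83% for first events.

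The episode count assumes that 1.5 per person-year holds for every episode, that rates are constant, and that loss to follow-up is handled as a flat 20% reduction, which is the accounting that reproduces 1315. The 18% to 19% is a share of events, not of statistical information. The two differ in a cluster trial, because the between-cluster part of the variance does not shrink as events accrue.

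**What to change.** - State in Sample size {14} and in the Primary subsection that the primary endpoint is all malaria episodes over 24 months, with the two-week off-risk window.
- Either restate the expected events and power on that basis, saying whether 1.5 per person-year is a first-event or an all-episode rate, or state that first-event sizing is a deliberate conservative simplification.
- Define the interim trigger in the unit of the primary model, with the information fraction that matches it, and check that the stopping boundaries still correspond.
- Report time to first event as a sensitivity analysis.

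The cost is wording in two sections and one re-run of the power and boundary calculations, with no added children, clusters or data. The headline event count and possibly the interim trigger would change, so this should be settled before any outcome data are examined.
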